## Abstract

**Background:**

Cardiovascular disease (CVD) is the main cause of mortality throughout the world. With accumulating evidence suggesting that CVD has its origins in childhood, it is unsurprising that research into obesity prevalence within school aged youth is burgeoning.

Within this study our primary objective will be to examine whether high intensity interval training (HIT) improves the CVD risk profile of secondary school aged adolescents. Our secondary objective will be to identify the prevalence of CVD risk factors and examine factors associated with these in adolescents aged 15 - 18 years.

**Method/Design:**

A South Lanarkshire school of low socioeconomic status (SES) was selected to participate in the study intervention. Participants from secondary 5 (15 - 17 years) and 6 (16 - 18 years) will be recruited for this study. Participants from secondary 6 will be randomly assigned to Group A (HIT) or Group B (moderate-vigorous) and will perform each protocol three times weekly. The secondary 5 participants will act as the control group. Data collection will take place during the Physical Education (PE) lessons and on school premises and will include: anthropometrical variables (height, weight, waist and hip circumferences, skinfold thickness at two sites), physiological responses (blood pressure, aerobic fitness, heart rate (HR) response, vertical jump performance, 10-metre (m) sprint, 50-m sprint and 505-agility test), diet (self-reported seven-day food diary), physical activity (Physical Activity Questionnaire for Adolescents (PAQ-A)) and blood tests (fasting glucose, insulin, total cholesterol (TC), high-density lipoprotein (HDL), high-sensitivity C-reactive protein (hs-CRP), fibrinogen (Fg), interleukin-6 (IL-6), adiponectin (high molecular weight), triglyceride and plasminogen activator inhibitor-1 (PAI-1). An environmental audit of the secondary school and the health related quality of life (HRQOL) of the participants will also be measured. Finally, all exercise sessions will be video recorded and rate of perceived exertion (RPE) and mood states will also be taken after each exercise session.

**Discussion:**

Our study may be able to demonstrate a time efficient means of reducing CVD risk factors in adolescents.

**Trial Registration:**

NCT01027156

## Background

The pandemic rise in overweight and obesity is now very much a global concern. Within the United Kingdom (UK), recent investigations denote worrying figures. In England it is estimated that 25% of adults are obese with an additional 40% overweight whereas in Scotland estimates indicate that 66% of adult males and 60% of adult females are either overweight or obese [1,2]. The findings concerning children and adolescents are equally troubling. Recent estimates from England purport that 14% of 2-15 year olds are obese while 18% are overweight [2]. Within Scotland estimates suggest that for 2-15 year olds, 35% of boys and 30% of girls are either overweight or obese [1]. Given the complexity of factors associated with both overweight and obese status within adults and children it is difficult to predict future trends. Recent findings seem to intimate that obesity levels in England's youth may be beginning to level off [3]. Though this is encouraging, and as the authors [3] contend, it is too early to confirm whether this is an ongoing trend. Others meanwhile suggest that if current trends are to continue unabated in the UK, 60% of men and 50% of women by the year 2050 will be classified as obese [4].

CVD is the main cause of mortality throughout the world with a reported 17.1 million deaths attributed to the disease in 2004, an astonishing 29% of global deaths in that year alone [5]. Though chronic disease may develop over an individual's lifetime, accumulating evidence suggest that CVD has its origins in childhood [6,7]. Findings from the longitudinal Bogulasa Heart Study [8] in the United States (US) found that 60% of 10 year old children who were overweight had at least one biochemical or clinical CVD risk factor. A further 25% had three or more. Considering that childhood overweight is a risk factor for severe obesity throughout life and is associated with morbidity and mortality of several diseases [9], it is unsurprising that research into obesity prevalence within youth is burgeoning. Particularly when recent reports estimate that 10% of all youth globally will become overweight [10] and that 80% of obese adolescents will become obese adults [11].

Numerous risk factors have been linked to the development of CVD. These include poor dietary habits, physical inactivity, obesity and overweight, hypertension and abnormal lipid profiles [6,7]. While these are well established, recent emergent biochemical risk factors have also been identified and include, most notably, elevated levels of hs-CRP, IL-6,; and reduced levels of adiponectin (high molecular weight) [12,13]. However, a number of these risk factors are modifiable.

Nevertheless, the relationship between physical fitness, PA, CVD risk factors, overweight and obesity is poorly understood in youth. Despite gathering evidence [14,15], there is still a need for further research that can strengthen this relationship, particularly as current PA recommendations for youth have been questioned [6]. This will not only help identify those in danger of future CVD but will also provide a means of assessing the effectiveness of future interventions.

### Physical activity and obesity prevention

Understanding the underlying factors and mechanisms whereby individuals become overweight or obese is challenging. There are a wide range of behavioural, genetic, cultural, environmental and biological variables that act both independently and amongst one another which contribute to the development of overweight and obesity in youth [16]. Nonetheless, it is generally accepted that two modifiable behavioural factors have contributed significantly to the aetiology of this current pandemic: dietary habits and PA [17,18]. While we fully acknowledge the key role of dietary intake in the aetiology of overweight and obesity, this study will primarily focus on modifying PA behaviour.

Despite the well established benefits of regular PA on health and well-being, current levels of PA in youth are widely regarded as insufficient to meet current recommendations [19]. Recent findings from the US purport that only 8% of adolescents (12 - 19 years of age) are sufficiently active to meet these recommendations [20]. In Europe, only one third of adolescents (11 - 15 years of age) meet the UK guidelines of 1 hour of moderate to vigorous intensity physical activity (MVPA) most days [21]. Though these findings are perturbing, caution in its interpretation is warranted.

For instance, PA in youth can occur in a variety of situations and contexts - through active commuting, recreation, school and in the household [22]. Given that the above author [22] has questioned the reliability, objectivity and validity of many of the methods used in assessing PA behaviour, current summations are inherently imprecise. Though evidence is gathering through advancements in technology and the use of more objective measures [23,24], much needed research is warranted. Until then, the extent of which youth of different age, gender and cultural climates are meeting current PA recommendations will remain unclear.

### Combating overweight and obesity in school age youth

It is now well established that PA behaviours are influenced by a range of various influences and as such, a multilevel approach targeting these influences are warranted [25]. This switch in focus however is relatively recent and at present, much is still to be learned of the multiple influences on PA behaviour. It has been suggested that in the past, researchers were too reliant on the dominant models and theories of behaviour which emphasized the importance of psychological and social influences [26]. While both of these influences are important, the field of PA research has now advanced by recognizing the importance of factors at multiple levels. This it seems has stemmed from the success of smoking cessation rates in the US from 1965 - 2005. This success has been attributed to a number of multi-level population based health behaviour interventions, all of which have been informed by the principles afforded by ecological models [27].

Ecological models profess that individual, interpersonal, organizational, societal and community factors should be considered when planning and implementing health promotion interventions [28]. It is unsurprising that traditional PA interventions rooted in a cognitive-rational paradigm which focus on changing behaviour at an individual level have demonstrated limited long-term success [29]. Though these interventions often alter behaviour initially, it is suggested that enduring social and environmental factors are more likely to sustain healthy PA behaviours [30]. Thus, interventions that can be directed at the whole community and encompass as large a percentage of the population must be the setting where future multilevel interventions are implemented. Schools afford the ideal setting to practice health-promoting behaviours, and are a critical part of the social environment that shape future behaviours [31]. With this in mind, the potential therefore of PE within schools to affect youth activity levels should not be dismissed.

### Physical activity and cardiovascular disease: the role of physical education

PE is available to most individuals and can provide a safe, structured context for regular PA. Despite this, evidence suggest that children and adolescents spend less that 50% of PE time in moderate intensity activity thus failing to procure any health related benefits [32]. While some have questioned the influence PE can have on overall activity levels [33], some suggest that activity levels would be even lower were youth not exposed to any [34]. What is becoming more evident nonetheless is that the intensity of PE classes are inappropriate to induce health related benefits [32]. The reasons for this are complex [33] but if PE is to be the only exposure to PA for some individuals, this environment has to enhance the health and well-being of those exposed to it. The challenge for practitioners therefore is to ensure that the stimulus provided is appropriate to induce health and well-being in all exposed individuals. Unfortunately, measuring the influence of PE on health and well-being is challenging.

The comparison of PA levels across the PE curriculum is nigh impossible due to confounding variables such as lesson delivery, teaching personnel, environment, equipment, motivation, skill ability, class size and time restrictions [35]. This is in addition to the difficulties associated with accurately measuring the intensity of activity. Recent advancements in technology has seen accelerometers being touted as an objective measure of exercise intensity by some authors [19,36]. However, accelerometers are unable to delineate between different behaviours such as walking or running. Understandably the relationship between school PE and health has been impossible to quantify. With the role of PE continually being marginalized within the educational curriculum, its justification as a contributor to health and fitness in youth is debatable.

Regrettably, the duration, type, and intensity of activity necessary to illicit cardiovascular and psychological health benefits in youth remains equivocal. There is insufficient clinical evidence to confirm that the recommendations proposed for children and adolescents (one hour per day of moderate activity) [37] has any short or long-term health benefits [38]. It is widely accepted that regular PA of this nature is necessary to accrue health benefits and prevent future CVD; nevertheless, the majority of youth fail to meet these current guidelines. Given that lack of time is commonly cited as a key determinant of being physically active regardless of age, gender or ethnicity [39] suggests that current recommendations may be inappropriate for youth.

To our knowledge there has been no empirical study that has directly compared how training strategies might affect the health status in youth. Accordingly, additional research seems warranted to determine whether there is a more time- efficient method of improving the health and fitness of youth. Recent findings suggest that brief intense, interval-based exercise interventions may stimulate cardiovascular adaptations and provide protection against future and current CVD [40-45]. Therefore, we propose a time efficient training regime which can be performed concurrently with the national curriculum and that will afford the measurement of health related outcomes. In particular, this study will aim to identify a time-efficient PA strategy for improving the health profile, CVD pre-cursers, overweight and obesity levels of youth in the UK.

We fully acknowledge that for this intervention to be successful, appreciation of the multiple influences upon behaviour is required. Indeed, a multilevel approach is needed for implementing population based health behaviour interventions that can enhance the health and well-being of individuals [25]. Thus, this pilot intervention will be influenced by the key principles afforded by ecological models. The findings of this study will be used to guide and enhance the effectiveness of future interventions at multiple levels within a school environment.

## Method/Design

### Objectives

This study will aim to implement a 7 week school based HIT intervention that will seek to enhance our understanding of the relationship between exercise intensity and health status in youth.

### Primary objectives

1. To reduce measures of obesity including body mass index (BMI), total skinfold thickness and waist and hip circumferences.

2. To reduce systolic and diastolic blood pressure.

3. To improve aerobic profiles and increase PA levels.

4. To improve blood lipid profiles and lower levels of plasma inflammatory markers.

5. To assess the impact of the HIT intervention on physiological responses.

6. To assess the role of a secondary high school as a setting for promoting healthy eating and PA behaviours.

7. To improve understanding of the multiple levels of influence on behaviour.

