### Data Analysis

A pre- and post-intervention design will be used to compare differences in measured outcomes between participants assigned to the control group and the intervention groups. Initially, baseline data will be used to perform Pearson's product moment correlation coefficients, followed by multiple regression analysis to estimate the significance of selected predictors on CVD risk factors. Statistical significance will be set at *P *= 0.05.

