#### Sample size

In order to determine sensitivity to change, sample size will be estimated using the procedures of Park and Schutz [67] for ANOVA designs that incorporate a repeated factor. For a medium effect size in the intervention groups of d = 0.50, power of .80 (suggesting an 80% probability of achieving significance at the *p *= .05 level) this is achieved with a group size of 17 participants. Effect sizes > 0.5 indicate clinically relevant changes [68]. Assuming a drop-out rate of 30%, this would require an initial recruitment of 24 participants per group. The intervention will be carried out during the lunch hour or PE lessons, on Monday, Wednesday and Friday, and for a period of 8 weeks. The interventions will be performed in the school sports hall; led initially by the research team and then by the PE teacher; and during January through May, 2009, to allow for uninterrupted use of the facilities.

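### Seven unranked primary objectives, with no primary outcome or contrast named and a sample size tied to none, leave a 34–64% chance of a nominally significant primary result if nothing works

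*Protocol article*

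**What the plan says.** **Objectives.** The Primary objectives section of the protocol article has seven numbered items without ranking. The first is "To reduce measures of obesity including body mass index (BMI), total skinfold thickness and waist and hip circumferences". Items 2 to 5 cover blood pressure, aerobic fitness and physical activity, blood lipids and inflammatory markers, and physiological responses. Items 6 and 7 concern the school as a setting and the levels of influence on behaviour. The abstract instead gives one primary objective, to "examine whether high intensity interval training (HIT) improves the CVD risk profile of secondary school aged adolescents", and no variable is defined for that profile.

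**Analysis.** The Data Analysis section compares measured outcomes before and after the intervention between the control group and the intervention groups. It then describes baseline correlations and regressions and ends: "Statistical significance will be set at" P = 0.05. The Intervention section describes three groups of 24: A (HIT) and B (moderate-vigorous) are randomised from secondary 6, and C, the control, is the secondary 5 pupils.

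**Sample size.** The basis is "For a medium effect size in the intervention groups of d = 0.50, power of .80", and "this is achieved with a group size of 17 participants". After allowance for drop-out: "Assuming a drop-out rate of 30%, this would require an initial recruitment of 24 participants per group". The section names neither the outcome nor the pair of groups to which the effect applies.

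**The concern.** Which outcome is primary, on which contrast, and what the sample size is meant to detect are decisions a protocol makes. Here they are made in a way that gives many outcomes equal primary standing. Nothing in the text would stop a report from presenting whichever of them fell below 0.05 as a primary finding. Nor could a reader tell whether the 80% power applies to that outcome. The abstract does not settle the matter, because its single objective has no measured variable behind it. What is at stake is the study's main conclusion, that HIT does or does not improve cardiovascular risk in adolescents.

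**Working it through.** **1. The plan's own figure.** The stated inputs are d = 0.50, power 0.80, level 0.05 and a repeated-factor ANOVA. I assume f = d/2 = 0.25, two groups, two time points and a correlation of 0.5 between them. With N = 34:

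λ = f² × N × 2/(1 − r) = 0.0625 × 34 × 2/0.5 = 8.5

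The interaction test on F(1, 32) then has power 0.807, so 17 per group is reproduced. For drop-out, 17/0.7 = 24.3, which agrees with 24 apart from rounding. No outcome enters this calculation.

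**2. Counting outcomes.** The protocol gives no count. This is a mapping of objectives to the measurements described.

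| Objective | Measures | Number |
|---|---|---|
| 1 | BMI, skinfolds, waist, hip | 4 |
| 2 | systolic and diastolic pressure | 2 |
| 3 | shuttle test, activity questionnaire | 2 |
| 4, narrow | total cholesterol, HDL, triglyceride, hs-CRP, IL-6 | 5 |
| 4, wide | the same plus fibrinogen, adiponectin, PAI-1 | 8 |
| 5 | nothing new; or jump, 10 m, 50 m, agility; or those plus heart rate and push-ups | 0, 4 or 6 |
| 6, 7 | descriptive, no between-group test | 0 |

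- Narrowest: 4 + 2 + 2 + 5 = 13.
- Wide objective 4, nothing new from objective 5: 4 + 2 + 2 + 8 = 16.
- Adding four performance tests: 20. Adding heart rate and push-ups: 22.

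**3. Chance of at least one P < 0.05 when nothing works.** Assume one two-sided test per outcome (sidedness is not stated). For K independent outcomes the chance is 1 − 0.95^K. Counting only results favouring HIT on one contrast, it is 1 − 0.975^K.

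- K = 13: 1 − 0.95^13 = 0.49; 1 − 0.975^13 = 0.28.
- K = 20: 1 − 0.95^20 = 0.64; 1 − 0.975^20 = 0.40.

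For correlated outcomes I simulated groups of 17 with equal correlation between outcomes and one contrast tested per outcome. The correlations are assumptions.

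| Outcomes | Either direction, correlation 0 / 0.3 / 0.5 | Favouring HIT, correlation 0 / 0.3 / 0.5 |
|---|---|---|
| 13 | 49% / 42% / 34% | 28% / 22% / 17% |
| 16 | 56% / 48% / 38% | 33% / 25% / 19% |
| 20 | 64% / 55% / 43% | 40% / 28% / 22% |

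One omnibus three-group test per outcome gives nearly the same either-direction figures (for 20 outcomes, about 54% at correlation 0.3 and 43% at 0.5). With 22 independent outcomes the either-direction figure is about 68%. The benchmark for one designated outcome and contrast is 5%, or 2.5% in the favourable direction.

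**4. All three pairwise contrasts, no gate.** For 20 outcomes: about 94%, 86% and 74% at correlations 0, 0.3 and 0.5.

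**5. Would later adjustment cure it?** Bonferroni over 20 outcomes uses 0.05/20 = 0.0025. Under the model in step 1, power at 17 per group falls from 81% to 38%, and about 33 evaluable per group would be needed.

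**The case against.** Several counter-arguments have force.

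- **Adjustment may be planned elsewhere.** A statistical analysis plan or full protocol, not shown, may handle multiplicity. This stands, so the absence of an adjustment is not the point here. The unranked list and the unattached sample size are on the page, and step 5 shows that adjusting across the whole list would not leave the stated power intact.
- **No success rule is written.** A reader might infer that any outcome crossing 0.05 counts as success. The protocol does not say so. The sentence on the level directly follows the baseline correlations and regressions, and the Sample size section repeats the level only as a planning input. What can be said is that no other level is given and nothing excludes that use.
- **The count is a reading.** A reader might take 20 outcomes as the minimum. The text does not support that: objective 4 speaks of lowering inflammatory markers, which does not fit adiponectin, and fibrinogen and PAI-1 are not called inflammatory. Thirteen is defensible.
- **The harm is directional.** A false claim for HIT needs a favourable result, which brings the figures down to 17–40%.
- **Abstract and list overlap.** The risk profile can be read as an umbrella for objectives 1 to 4, so this is a lack of definition more than a flat contradiction.
- **It is called a pilot.** The Background does say so, but the Sample size section plans for "suggesting an 80% probability of achieving significance at the" 0.05 level, and the abstract makes efficacy the primary aim.

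**Conclusion.** The point holds as a matter of how the protocol fixes its primary question. Seven unranked objectives, about 13 to 22 outcomes under five of them, three groups, no named primary outcome or contrast, and a sample size belonging to none of them do not define a primary test. With one test per outcome at 0.05, the chance of at least one nominally significant primary result when nothing works is about 34–64% (13–20 outcomes, correlation 0.5 to 0). It is about 17–40% for results favouring HIT on one contrast. These figures rest on the mapping of objectives to measurements, equal correlations, and two-sided tests in groups of 17.

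A reader might go further and call a false positive likely, or quote the 74–94% for all pairwise contrasts. The documents do not support either as a general statement. Much of the one-test range lies below one half, as does the whole favourable-direction range. The pairwise figures assume ungated testing that the protocol does not describe. Comparisons with group C are also non-randomised, so their true error rate may exceed these figures by an amount the documents do not allow one to calculate.

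**What to change.** - **Primary outcome.** In Primary objectives, name one outcome built from data already collected. A clustered cardiovascular-risk z-score, with components and scoring fixed in advance, would match the abstract.
- **Primary contrast.** Name one contrast, tested at 0.05. A versus B is preferable because it is the randomised comparison; group C differs from both by school year as well as by treatment. This makes the primary question whether HIT does better than moderate-vigorous exercise, and the abstract should then say so.
- **Sample size.** State the 0.50 effect and the 17 per group for that outcome and contrast, and recheck that 17 suffices for them.
- **Other outcomes.** Make them secondary, with Holm or false-discovery-rate control within families (anthropometry, blood pressure, blood markers, fitness), or label them exploratory.
- **Objectives 6 and 7.** Move them to descriptive aims.

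This brings the false-positive rate for the primary test to 5%. It is a change of wording and needs no new measurements. The cost is that fewer outcomes can be claimed as primary successes, and adjusted secondary outcomes have somewhat lower power.
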